## Secondary Objective(s)

| **Secondary Objective** | **Endpoint(s)** | **Time Frame** |
| --- | --- | --- |
| 1. Assess feasibility and acceptability of measuring biochemically-verified 7-day point months follow-up at 3 months | Evaluate the proportion of participants who achieve biochemically-verified 7-day point prevalence abstinence defined as participants (1) reporting not smoking a single cigarette in the past seven days, not even a puff; and (2) having CO levels ≤5 ppm | Baseline to 3 months |
| 1. Assess feasibility and acceptability of measuring prolonged abstinence at 3 months and 6 months follow-up | Evaulate the proportion of participants who achieve prolonged abstinence defined as participants (1) not smoking a single cigarette since the last visit; (2) having CO levels ≤5 ppm. | Baseline to 3 months, and baseline to 6 months follow-up |
| 1. Assess feasibility and acceptability of measuring 12 point prevalence abstinence | Proportion of participants who achieve biochemically-verified 7-day point prevalence abstinence defined as participants (1) reporting not smoking a single cigarette in the past seven days, not even a puff and (2) having CO levels ≤5 ppm. | Baseline to 12 months follow-up. |

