
# Introduction

## Background

Cigarette smoking is exceedingly common among people experiencing homelessness, with a prevalence of 70% compared to 13.7% in the general population.^1,2^ Severe mental illness and substance use disorders are common among homeless adults and are risk factors for smoking and for poor smoking-related health outcomes.^3^ Smoking-induced cardiovascular diseases and cancers are the leading causes of morbidity and mortality among homeless adults.^4-8^

Homeless adults make quit attempts as frequently as the general population, but they are less successful at quitting completely.^9-11^ The quit ratio (former/ever smokers), a measure of successful quitting, among homeless adults is between 9% and 13%,^11,12^ almost 5 times lower than the general population (~61%).^2^ Clinical trials of behavioral counseling and pharmacotherapy—the standard care for smoking cessation—have failed to demonstrate substantial long-term abstinence among homeless adults.^13-17^ Long-term abstinence, defined as abstinence for 6 months or more, is a strong predictor of successful cessation.^18^ Behavioral counseling and pharmacotherapy alone may be insufficient to promote long-term abstinence, which is necessary to increase cessation rates among this population.

Cessation interventions not only need to be efficacious in clinical trials, but also scalable to practice settings.^19,20^ Although there have been randomized controlled trials (RCT) of cessation interventions for homeless adults, these trials have not been tested in practice-based settings. The majority of homeless adults in the U.S. seek health care in federally-funded, safety net community health centers. Safety net health clinics that provide care to homeless adults could bring cessation interventions to scale.

Research is needed to 1) identify interventions that can increase the effect of behavioral counseling and pharmacotherapy on long-term abstinence (≥6 months) among homeless adults; and 2) determine how such interventions can be brought to scale in safety net clinics serving homeless adults. As a step toward answering those questions, we will pilot test a RCT of a contingency management smoking cessation intervention for homeless adults seeking care in a safety net health clinic.

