# Study Design

## Characteristics

This is a phase I single site RCT of an extended contingency management intervention for smoking cessation for people experiencing homelessness and who are engaged in clinical care at the Tom Waddell Urban Health Clinic (TWUHC), Richard H. Fine People’s Clinic (RFPC), or the Positive Health Program (PHP) Clinic. Participants will be recruited from the TWUHC, RFPC, and PHP, and study procedures will take place at the Civic Center Plaza or at the Zuckerberg San Francisco General Hospital (ZSFG) courtyard to minimize risk from gathering in indoor locations during the COVID-19 pandemic. We will randomize 45 participants to the intervention arm and 45 participants to the control arm. Participants will receive usual cessation care at TWUHC, RFPC, or PHP, that includes weekly behavioral counseling and pharmacotherapy. The intervention will include the provision of financial incentives contingent on biochemically-verified abstinence for up to 6 months, with a potential to earn up to $620 in contingent reinforcements for cessation. Control group participants will receive $5 for attending each abstinence assessment. Participants will be asked to choose a quit date within 7 days of providing consent, and will meet study staff at TWUHC, RFPC, or PHP on the day of the quit attempt. Participants will meet daily for the first 7 days (week 1), twice weekly for the next 3 weeks (1 month), once weekly for the next 9 weeks (3 months), and monthly until the one-year follow-up (1 year). Assessment visit schedule is identical for both groups. At each of the scheduled assessment visits, participants will provide a CO sample and complete a short questionnaire on cigarette consumption, quit attempts since the last visit, the length of the last quit attempt, and use of medications and services. Questionnaires will be built on REDCap, and administered by study staff using an iPad. At enrollment, 2 weeks, 1 month, 3 months, 6 months, and 1-year follow-up, participants will be asked to complete structured questionnaires. The final study follow-up will be at 1 year.

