# Study Intervention

## Administration and/or Delivery of Study Intervention

**Usual smoking cessation care at TWUHC, RFPC, and PHP**. Patient participants will be required agree to attend usual smoking cessation care that is available to all clinic patients who receive clinical services at the clinic. Usual cessation care includes weekly one-on-one counseling by on-site behavioral counselors and pharmacist-dispensed NRT (i.e., transdermal patch, the gum or lozenge, the primary cessation medications in this clinical trial) covered by health insurance for at least 12 weeks.

| **Table 1: Escalating Contingency Management Schedule for Intervention Group^** | | | | |
| --- | --- | --- | --- | --- |
|  | Visit frequency | # of Visits | Intervention group potential earnings | |
|  |  |  | Total for time period | Average per visit |
| Week 1 | Daily | 7 ($13.00-16.00) | $101.50 | $14.50 |
| Weeks 2 – 4 | Bi-weekly | 6 ($16.50-19.00) | $106.50 | $17.75 |
| Weeks 5 – 13 | Weekly | 9 ($19.50-23.50) | $193.50 | $21.50 |
| Weeks 14– 24 | Monthly | 3 ($24.00-25.00) | $73.50 | $24.50 |
| Total (6 months) |  | **25** | **$ 475** |  |
| ^ Incentive payment begins @ $13.00 and increases by $0.50 for each consecutively negative CO sample (<5 ppm) to a maximum of $24.50 for the last sample. | | | | |

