#### Visits 24-26 (Weeks 16-24)

- Review of concomitant medications
- Adverse Events assessment
- Administration of Study Intervention: Contingent incentives for smoking cessation
- Protocol-specific assessments/procedures: Expired carbon monoxide sample and a brief questionnaire monthly between 3 and 6 months; Questionnaires at 6 months follow-up; At 6 months follow-up, if participants self-report abstinence, and have an expired carbon monoxide level < 5ppm, then we will collect a urine sample for anabasine/anatabine analysis.

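### Prolonged abstinence is assessed only back to the last visit: on the plain reading, 7 days at 3 months and about 26 to 28 days at 6 months

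*Protocol*

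**What the plan says.** Section 2.2 of the protocol lists the objective "Assess feasibility and acceptability of measuring prolonged abstinence at 3 months and 6 months follow-up". The endpoint is the proportion with "prolonged abstinence defined as participants (1) not smoking a single cigarette since the last visit; (2) having CO levels ≤5 ppm", and the time frame column reads "Baseline to 3 months, and baseline to 6 months follow-up". The row above, for 3 months, is 7-day point prevalence abstinence with the same CO limit.

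Section 3.1 gives the visit schedule: daily in week 1, twice weekly for three weeks, then "once weekly for the next 9 weeks (3 months), and monthly until the one-year follow-up (1 year". Section 3.1, Section 5.1 (abstinence assessment schedule) and the opening of Section 6 all describe a short questionnaire given at every assessment visit. Its question on quit attempts looks back to the last visit.

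No section gives a start date or a grace period for prolonged abstinence, or requires abstinence at earlier visits. Section 5.1, on outcomes for the future full-scale trial, names prolonged abstinence at each follow-up visit and points to published guidelines without stating a look-back.

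**The concern.** The name of the endpoint suggests abstinence sustained over a long stretch. The rule asks only about the interval since the preceding visit, and the visit schedule sets the length of that interval. Someone who smoked through week 11 and stopped by the week-12 visit would count as prolonged abstinent at week 13.

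Three things follow:

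- The 3-month result can nearly repeat the 7-day point prevalence result while carrying a stronger label.
- The 3- and 6-month results cover windows of different length, so they cannot be read as one measure over time.
- If the last visit means the last one attended, a participant who missed visits must have been abstinent for longer than one who attended.

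The intervention is meant to promote abstinence of 6 months or more (Sections 1.1 and 1.3). The proportion continuously abstinent to each time point is therefore the figure a reader would expect under this name.

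**Working it through.** **Inputs.** Table 1 (Section 5.1) gives 7 daily visits in week 1, 6 visits in weeks 2 to 4, 9 weekly visits in weeks 5 to 13 and 3 monthly visits in weeks 14 to 24. Section 6.2.2 places the three monthly visits in weeks 16 to 24. Section 1.4 lists the longer follow-up visits at 2 weeks, 1, 3 and 6 months and 1 year.

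**The plan's own figure.** 7 + 6 + 9 + 3 = 25 visits, as Table 1 states.

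**Formula.** Look-back = day of the time-point visit minus day of the previous scheduled visit. Days are counted from the quit date, with week 13 as 3 months and week 24 as 6 months.

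**Plain reading (previous assessment visit, attended).**
- 3 months: 13 × 7 − 12 × 7 = 91 − 84 = 7 days; 7/91 = 8%.
- 6 months, visits at weeks 16, 20 and 24: 168 − 140 = 28 days; 28/168 = 17%.
- 6 months, three visits spread evenly over the 11 weeks after week 13: (11/3) × 7 = 25.7 days; 25.7/168 = 15%.

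**Alternative reading (previous longer follow-up visit).**
- 3 months, back to the 1-month visit at week 4: 91 − 28 = 63 days; 63/91 = 69%.
- 6 months, back to the 3-month visit at week 13: 168 − 91 = 77 days; 77/168 = 46%.

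| Reading | 3 months | 6 months |
| --- | --- | --- |
| Previous assessment visit | 7 days | about 26 to 28 days |
| Previous longer follow-up visit | 63 days | 77 days |
| From the quit date | 91 days | 168 days |

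**Effect of one missed visit, if the last attended visit counts.** Missing week 12 makes the 3-month window 91 − 77 = 14 days. Missing week 20 makes the 6-month window 168 − 112 = 56 days. Missed visits are expected: the adherence threshold in Table 2 (Section 5.4) is a CO sample at 14 to 17 of 25 visits, which leaves 8 to 11 without one.

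**Overlap at 3 months.** With the week-12 visit attended, both endpoints require no smoking over 7 days and CO ≤5 ppm at week 13. At 6 months a window of about four weeks is clearly different from 7 days, so the overlap does not extend there.

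**Check on schedule inconsistencies.** Appendix 1 gives 8 weekly weeks where Section 3.1 gives 9, and the table in Section 6.1 numbers the weekly visits 15 to 22 where Section 6.2.2 has 15 to 23. Visits in that block stay weekly, so the 7-day gap is unaffected.

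**The case against.** The strongest reply is that the look-back is ambiguous, not fixed at 7 days. Section 1.4 separates the longer follow-up visits from the brief assessment visits, and this endpoint is set at follow-up time points. Read that way, the windows are 63 and 77 days and the overlap with 7-day point prevalence disappears. This reading is possible but less natural, because the protocol uses the same phrase for the questionnaire at every assessment visit. It also falls short of the period from the quit date, so it does not cure the problem.

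Several stronger inferences are tempting, and the documents do not support them:

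- **The pilot yields no information on sustained abstinence.** Section 2.3 lists longest duration of abstinence over 6 months, and Section 5.1 describes it as a count of uninterrupted days. That is related information, though not the proportion continuously abstinent to 3 or 6 months.
- **The definition will pass into the full-scale trial.** Section 5.1 refers that trial's outcome to published guidelines and does not repeat the wording of Section 2.2.
- **The time frame column contradicts the definition.** The same baseline-to form is used for the 7-day point prevalence rows, so it sets no look-back.
- **The background section defines the term.** The sentence "Long-term abstinence, defined as abstinence for 6 months or more, is a strong predictor of successful cessation" concerns a different term.
- **The window differs by arm.** Controls are paid for attending and intervention participants for negative CO, so attendance could differ, but the protocol gives no attendance figures by arm.

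The objection on importance stands. Section 9.3 plans descriptive analysis only, and no threshold in Table 2 uses prolonged abstinence. A statistical analysis plan could settle missing detail, but here the protocol itself states the rule.

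**Conclusion.** The concern holds as a faulty definition of a secondary endpoint. On the plain reading it covers 7 of about 91 days at 3 months and about 26 to 28 of about 168 days at 6 months. At 3 months it is in substance the 7-day point prevalence endpoint for participants who attended the previous weekly visit, and otherwise its window varies with attendance. On the less natural reading it covers about 63 and 77 days. On neither reading does it report the proportion continuously abstinent to 3 or 6 months.

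The figures assume that the previous scheduled visit was attended, that the time points fall at weeks 13 and 24, and that the monthly visits are at weeks 16, 20 and 24 or evenly spaced. The primary objective and the feasibility decision do not depend on this endpoint. What is at stake is how the result is labelled and understood.

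**What to change.** Replace the look-back in Section 2.2 with a fixed calendar window. Count a participant as prolonged abstinent at 3 or 6 months if all of these hold:

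- no self-reported smoking from the quit date to the time point;
- CO ≤5 ppm at the time-point visit;
- no CO above 5 ppm at any attended visit in between.

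For a missed interim visit, use the self-report at the next attended visit, asked so that it covers the whole gap. Count a missing time-point visit as not abstinent. If a grace period is wanted, fix one length before analysis; it decides how samples from the first days after the quit date count.

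Report by arm the number of CO samples behind each classification. Biochemical verification still depends on attendance, since a participant with fewer visits faces fewer tests.

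Smoking questions and CO are already part of every assessment visit, so the cost is wording and a little more derivation work. The reported rate will be lower than under the current rule.

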# Study Objectives and Endpoints

## Primary Objective

| **Primary Objective** | **Endpoint(s)** | **Time Frame** |
| --- | --- | --- |
| 1. Assess feasibility and acceptability of measuring biochemically-verified point prevalence abstinence at 6 months follow-up. | Evaluate the proportion of participants who achieve biochemically-verified 7-day point prevalence abstinence defined as participants (1) reporting not smoking a single cigarette in the past seven days, not even a puff; (2) having CO levels ≤5 ppm, and (3) anatabine/anabasine assays <2 ng/ml. | Baseline to 6 months follow-up |
| 1. Assess feasibility and acceptability of adhering to the protocol | Total number of carbon monoxide negative samples | Baseline to 6 months follow-up |
| 1. Assess feasibility and acceptability of gathering information on the number of visits attended | Total number of visits attended | 6 months |
| 1. Assess feasibility and acceptability of the retention protocol | Proportion of the sample retained as a result of retention procedures | 2 weeks, 1 month, 3 months, 6 months, and 12 months follow-up |

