**Abstinence assessment schedule*.*** All other aspects of the study protocol will be identical across the two experimental groups. Participants will be asked to choose a quit date within 7 days of providing consent,^26,30,32,33,100^ and will meet study staff at TWUHC or ZSFG on the day of the quit attempt (Table 1). Participants will meet daily for the first 7 days (week 1), twice weekly for the next 3 weeks (1 month), once weekly for the next 9 weeks (3 months), and monthly until the one-year follow-up (1 year). Assessment visit schedule is identical for both groups. At each of the scheduled assessment visits, participants will provide a CO sample and complete a short questionnaire on cigarette consumption, quit attempts since the last visit, the length of the last quit attempt, and use of medications and services. Questionnaires will be built on REDCap, and administered by study staff using an iPad.

***Abstinence assessment.*** As in prior studies, ^26,30,32,33,100^to determine eligibility for CM, we will assess point-prevalence abstinence with CO monitoring, using a cut-off of CO≤ 5 parts per million (ppm).^98^ For primary outcome assessment, we will confirm abstinence among participants who self-report abstinence and meet criteria for abstinence based on CO with urinary anatabine and anabasine (i.e. metabolites of tobacco) using a cut-off of <2 ng/ml ^101^ (analyzed by the UCSF Cancer Center Tobacco Biomarkers Core ^102^). Urinary anatabine and anabasine are tobacco alkaloids that are useful as confirmatory biomarkers to verify abstinence among patients who are using NRT for smoking cessation, and for whom urinary cotinine would not be appropriate.^101^

**Data collection reimbursements*.*** We will reimburse all participants with $20 for completing the baseline questionnaire, $15 each for questionnaires at 2, weeks, 1 month, and 3 months, and $25 each for questionnaires at 6 months and 1-year follow-up. Between 6 and 12 months, all participants will receive $5 for checking in at each monthly visit and providing a CO specimen. The total amount that all participants could earn for 1 year of participation exclusive of CM is $145 and as much as $620 inclusive of CM ($145+$475).

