**Clinical outcomes for the future full-scale RCT*.*** The primary outcome for the subsequent full-scale RCT will be biochemically-verified 7-day point prevalence abstinence at 6 months. Biochemically-verified 7-day point prevalence abstinence is defined as participants (1) reporting not smoking a single cigarette in the past seven days, not even a puff; (2) having CO levels ≤5 ppm, and (3) anatabine/anabasine assays <2 ng/ml. Secondary outcomes include 7-day point prevalence abstinence at 2 weeks and 3 months, and prolonged abstinence at each follow-up visit as per recent guidelines.^122^ We will also assess total number of CO-negative samples, longest duration of abstinence (i.e., total number of un-interrupted days of abstinence), total number of visits attended, and cigarette consumption for those unable to quit between the treatment groups. We will evaluate abstinence at 1 year to assess this outcome 6 months after incentives stop. In this pilot, we will assess the feasibility and acceptability of collecting each of these outcomes.

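### At 6 months, prolonged abstinence omits the urine assay that 7-day abstinence requires, so a participant can pass the longer claim and fail the shorter one at the same visit

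*Protocol*

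**What the plan says.** The Primary Objective table (Section 2.1) defines 7-day point prevalence abstinence at 6 months by three criteria: self-report of no smoking in the past seven days, then "having CO levels ≤5 ppm, and (3) anatabine/anabasine assays <2 ng/ml".

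The Secondary Objective(s) table (Section 2.2) defines prolonged abstinence by two: "not smoking a single cigarette since the last visit; (2) having CO levels ≤5 ppm". Its time frame is "Baseline to 3 months, and baseline to 6 months follow-up", so one definition serves both visits. The other two secondary rows, 7-day abstinence at 3 and at 12 months, also use self-report and CO only.

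Under Administration and/or Delivery of Study Intervention, the assay is tied to one outcome: "For primary outcome assessment, we will confirm abstinence among participants who self-report abstinence and meet criteria for abstinence based on CO with urinary anatabine". The same section, describing the full-scale trial, lists "prolonged abstinence at each follow-up visit as per recent guidelines" as a secondary outcome and names no assay for it.

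The procedures for Visits 24-26 (Weeks 16-24) collect urine at 6 months from participants who report abstinence and "have an expired carbon monoxide level < 5ppm, then we will collect a urine sample for anabasine/anatabine analysis". That trigger is strictly below 5 ppm, whereas both endpoint definitions admit exactly 5 ppm.

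**The concern.** Prolonged abstinence is the more demanding claim. Someone who has not smoked since the last monthly visit has not smoked in the past week, so the prolonged abstainers at a visit should be a subset of the 7-day abstainers at that visit. As defined at 6 months they need not be. A urine result showing tobacco exposure fails the participant on the weaker claim and is ignored on the stronger one, although for most of these participants the result has been obtained.

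At stake is the coherence of two abstinence figures reported from one visit. The pilot also tests whether these outcomes can be collected for the full-scale trial, so an incoherent definition would be carried forward with them.

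**Working it through.** No sample size, power or test statistic is involved. The check is whether one definition implies the other.

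**Step 1: self-report.** The 6-month visit is the last of three visits in weeks 16 to 24, with a "brief questionnaire monthly between 3 and 6 months". The spacing is (24 − 16)/2 = 4 weeks, or 28 days, which exceeds 7. No smoking since the last visit therefore implies none in the past seven days. This assumes that both items are answered to the same standard; the 7-day item says that a puff counts, and the prolonged item is silent on this.

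**Step 2: biochemical criteria at 6 months.**

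| Criterion | 7-day abstinence | Prolonged abstinence |
| --- | --- | --- |
| Self-report | none in 7 days | none since last visit |
| CO | ≤5 ppm | ≤5 ppm |
| Anatabine/anabasine | <2 ng/ml | not required |

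**Step 3: enumeration.** There are three feasible self-report patterns: none since the last visit; some since the last visit but none in 7 days; some in the past 7 days. Cross these with CO of 4, 5 or 6 ppm and an assay that is below 2, at or above 2, or missing: 3 × 3 × 3 = 27 states.

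- As written, the states that are prolonged abstinent but not 7-day abstinent are: 1 self-report pattern × 2 CO values (4, 5) × 2 assay values (≥2, missing) = 4 of 27.
- With the assay required for 6-month prolonged abstinence as well: 0 of 27.

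The two states with an assay at or above 2 ng/ml follow directly from the text. The two with a missing assay depend on counting a missing assay as failing the 7-day outcome. One of them, CO of exactly 5 ppm with no urine, is produced by the protocol's own collection trigger.

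**Step 4: effect on the proportions.** With a common denominator, prolonged % − 7-day % = (% discordant as in Step 3) − (% who meet the 7-day definition but smoked earlier since the last visit). The prolonged figure exceeds the 7-day figure whenever the first term is the larger.

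**Step 5: size, by assumption only.** The documents give no assay-failure rate. Suppose 10 participants in an arm meet the prolonged definition and each fails the assay independently with probability f. The expected number discordant is 10f, and the chance of at least one is 1 − (1 − f)^10.

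| f | Expected discordant | Chance of at least one |
| --- | --- | --- |
| 5% | 0.5 | 40% |
| 10% | 1.0 | 65% |
| 20% | 2.0 | 89% |
| 30% | 3.0 | 97% |

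**The case against.** The strongest defence is that the protocol follows a rule. It ties the assay to the primary outcome, and all three secondary rows consistently rest on CO alone. Stricter verification for the primary outcome is a legitimate choice, and one CO-only definition keeps prolonged abstinence comparable between 3 and 6 months. Both points stand as far as they go. The choice may be deliberate, but it leaves the two 6-month outcomes incoherent. The comparability point is a real cost of adding the assay at 6 months only, and the fix has to meet it.

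The defence is also right that little rides on this in the pilot. The outcome is secondary, and the Statistical Analysis Plans section proposes no inferential statistics.

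A reader might go further and infer bias between arms: intervention participants are paid on CO results while controls are paid for attending, so CO-negative but tobacco-exposed participants might cluster in the intervention arm and the CO-only outcome might overstate a benefit passed to the full-scale trial. The documents do not support this. They give no exposure data by arm, and Sample Size and Power Estimate bases future effect sizes on clinically important differences in the primary abstinence outcomes, not on pilot estimates.

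Nor can arithmetic supply the evidence. Suppose 15/45 and 7/45 pass self-report and CO, a difference of 17.8 points. Equal 10% disconfirmation gives (13.5 − 6.3)/45 = 16.0 points. Larger shrinkage, to (12 − 6.3)/45 = 12.7 or (10.5 − 6.3)/45 = 9.3 points, appears only if disconfirmation of 20% or 30% in the intervention arm against 10% in control is assumed at the outset.

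A reader might also infer that every candidate for 6-month prolonged abstinence already has a urine result. At exactly 5 ppm the visit procedures do not collect one.

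**Conclusion.** The mismatch is real and follows from the two definitions. At 6 months, and only then, a participant can be counted as prolonged abstinent while failing 7-day abstinence, and the prolonged proportion can exceed the 7-day proportion. At 3 months both outcomes rest on CO alone, so the problem does not arise; at 12 months the 7-day outcome is CO-only and no prolonged outcome is listed in the objectives.

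The number of participants affected, and whether it differs by arm, are unknown. The 0.5 to 3 per arm shown above rests on an assumed 10 abstainers and an assumed 5% to 30% failure rate. The point is a definitional correction to a secondary, descriptive outcome. It is worth making before the definition passes to the full-scale trial. It is not evidence of an overstated treatment benefit.

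**What to change.** - In Section 2.2, split the prolonged-abstinence definition by visit. At 6 months, add a third criterion: anatabine/anabasine below 2 ng/ml at that visit. Leave the 3-month definition as it is.
- Make the same addition where Administration and/or Delivery of Study Intervention describes the full-scale trial's outcomes.
- State that a missing 6-month assay is scored for prolonged abstinence in the same way as for the primary outcome.
- Also report the CO-only 6-month prolonged rate beside the assay-confirmed one, so that a change from 3 months is not confused with a change in verification.
- Reconcile the urine-collection trigger under Visits 24-26 with the endpoint cut-off, so that participants at exactly 5 ppm have an assay.

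The cost is a few lines of protocol text, one extra descriptive line in the report, and a few urine samples from participants at exactly 5 ppm. The 6-month prolonged proportion may be slightly less favourable.
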